## Abstract

**Introduction:**

The WHO recommends antenatal calcium supplementation (1500–2000 mg/day) to prevent pre-eclampsia in settings with low dietary calcium intake. Implementation is limited partly due to the need for three daily doses, although a lower 500 mg dose may be non-inferior. Current guidelines also recommend separating calcium from iron-containing supplements because concurrent intake may inhibit iron absorption. This individually randomised, controlled, non-inferiority trial will test whether co-administration of calcium and multiple micronutrient supplement (MMS) (CaMMS) is non-inferior to separate administration for haematological and iron status.

**Methods and analysis:**

We will recruit 1600 women at 6<20 weeks’ gestation in Burkina Faso and Pakistan, evaluating non-inferiority independently in each setting, which differ in anaemia aetiology and diets. Participants will be randomly assigned to (a) take United Nations International Multiple Micronutrient Antenatal Preparation Multiple Micronutrient Supplements (30 mg elemental iron) and 500 mg elemental calcium together in the morning or (b) take MMS in the morning and calcium in the evening. Venous blood will be collected at 6<20, 20<24, and 30<34 weeks’ gestation to measure complete blood count, ferritin, soluble transferrin receptor, hepcidin and erythropoietin. The primary outcome is haemoglobin concentration at 30<34 weeks. Co-administration will be considered non-inferior if the lower bound of the 95% CI for the difference in haemoglobin exceeds the non-inferiority margin of –3 g/L. Enrolment commenced in Pakistan on 25 August 2025 and in Burkina Faso on 12 September 2025.

**Ethics and dissemination:**

This protocol was approved by the Johns Hopkins School of Public Health Institutional Review Board, the Comité d’Ethique pour la Recherche en Santé, the Aga Khan University Ethics Review Committee and the Pakistan National Bioethics Committee. Findings will be disseminated through in-country meetings and in the peer-reviewed literature.

**Trial registration number:**

NCT06568315.

STRENGTHS and LIMITATIONS OF THIS STUDYThe calcium and multiple micronutrient supplement (CaMMS) non-inferiority trial testing the impact of co-administering calcium and MMS on haemoglobin and iron status will include sites in both Sub-Saharan Africa and South Asia, enhancing external validity and capturing diverse anaemia aetiologies and background calcium intakes that may influence the nutrient-nutrient interaction.The separate administration arm introduces greater complexity that could affect adherence; however, this is mitigated through intensive adherence promotion at monthly dispensing and household visits and further strengthened by unannounced mid-day household visits to assess real-world supplement consumption patterns despite the lack of direct observation.Although the trial is not powered for secondary outcomes such as anaemia, iron deficiency and pregnancy outcomes, it is adequately powered for the primary non-inferiority endpoint, which is the main objective informing policy-relevant conclusions.

## Introduction

 Women of reproductive age in low-and-middle-income countries typically consume diets inadequate in many micronutrients.^1^ Micronutrient deficiencies resulting from inadequate intakes are further exacerbated during pregnancy by the increased demands of the developing fetus.^2^ Currently, the WHO recommends daily iron and folic acid (IFA) supplementation with 30 mg to 60 mg of elemental iron and 400 µg of folic acid during pregnancy.^3^ This recommendation is motivated by the burden of anaemia during pregnancy, the specific demand of pregnancy for iron and iron transfer to the fetus. However, they acknowledge that many countries are transitioning from IFA to United Nations International Multiple Micronutrient Antenatal Preparation Multiple Micronutrient Supplements (UNIMMAP MMS or MMS), which includes 15 micronutrients in amounts needed during pregnancy.^4^ Compared with IFA supplementation, MMS improves maternal micronutrient status and increases micronutrient transfer to the fetus.^5–11^ Studies have also revealed a significant reduction of 15% in low birth weight (LBW), 7% in small-for-gestational age (SGA) births, 9% in stillbirth, 19% in early preterm birth (<34 weeks’ gestation) and weaker evidence of a 4% reduction in preterm birth.^12
13^ For countries electing to use MMS in place of IFA, WHO recommends that this action be accompanied by additional research,^4^ for example, on the feasibility, acceptability and cost-effectiveness of MMS versus IFA.

The current formulation of MMS does not contain calcium. Low dietary calcium intake is associated with hypertensive disorders of pregnancy and preeclampsia,^14^ which causes 40 000 maternal deaths annually worldwide.^15^ A 2018 Cochrane meta-analysis of 27 calcium trials^16^ showed that calcium in doses ≥1 g for women with low dietary calcium intake reduced high blood pressure by 35%, preeclampsia by more than half and death or serious morbidity by 20%. The Cochrane review also reported that daily doses of ≥1 g also reduced preterm birth by 24% but had no effect on SGA. In addition to IFA or MMS, WHO recommends that women with low-calcium diets receive 1.5–2.0 g daily in divided doses of 500 mg.^17^ This recommendation has not been widely implemented,^18^ likely due to the cost of supplements and adherence challenges with divided doses. A recently completed non-inferiority (NI) trial carried out in India and Tanzania indicated that a daily 500 mg dose is non-inferior to the higher dose in preventing preeclampsia.^19^ Results from the site in India also suggested that it was non-inferior for the preterm birth outcome.^19^

Given the new evidence that a 500 mg calcium dose is non-inferior to 1500 mg for key public health outcomes,^19^ there is increasing interest in modifying the MMS formulation to include 500 mg elemental calcium. A remaining challenge is that WHO recommends that calcium supplements be taken separately from iron-containing supplements because concurrent ingestion may reduce iron absorption.^17^ However, this supposition was largely based on evidence from studies of iron absorption from single test meals or short-term bioavailability.^20–25^ A 2021 meta-analysis found that, while there was a significant association between the use of calcium supplements and lower serum ferritin concentration, this did not translate into a difference in haemoglobin (Hb) concentration.^26^ It is important to note that most studies had specifically excluded pregnant women and were primarily carried out in high-income country settings, where baseline iron status was likely higher.^26^

A definitive study regarding the impact of concurrent iron and calcium supplementation on the haematological and iron status during pregnancy is an important next step towards the development of a single antenatal supplement that would increase uptake of and adherence to both interventions. The overall goal of the CaMMS trial is to evaluate the impact of co-administration of calcium and MMS, relative to separate administration, on Hb concentration and iron status of pregnant women and their infants.

## Methods and analysis

### Study design

This is an NI trial designed to assess the impact of UNIMMAP MMS and Ca (500 mg) taken concurrently, relative to taking them separately, on haematological and iron status of women and infants. Women will be individually randomised in a 1:1 ratio to take both supplements in the morning (‘together’) or to take the MMS in the morning and the calcium in the evening (‘separate’). Counselling messages and supplement packaging will not enable blinding of participants or study staff with direct participant contact. However, laboratory staff measuring the trial’s outcomes and investigators not directly involved in field work will be blinded. The code will be broken when all outcomes have been assessed. Enrolment commenced in Pakistan on 25 August 2025 and in Burkina Faso on 12 September 2025. Assuming an 8-month recruitment period for Burkina Faso and a 12-month period for Pakistan, we anticipate that field work will be completed by May 2027.

### Study setting

In Burkina Faso, the study will be conducted in Sandbongtenga Province, approximately 100 km northeast of Ouagadougou. The province’s altitude ranges from 350 to 400 m, while rainfall varies between 600 and 750 mm per year. The area is in a highly endemic malaria transmission zone.^27^ Malaria accounts for 57% of hospitalisations and 36% of deaths in health facilities in Burkina Faso. Four out of five cases are due to *Plasmodium falciparum*. Malaria is highly prevalent during the rainy season. Women will be recruited from three antenatal care clinics in Kaya district and two rural medical centres in the neighbouring Boussouma district.

In Pakistan, pregnant women will be recruited from the rural district of Thatta, located 103 km southeast of Karachi in Sindh Province. The district lies within the lower Indus River basin and is predominantly a low-altitude coastal plain, with elevations generally close to sea level. Malaria transmission in Thatta is endemic and follows the seasonal pattern observed across Sindh Province. Notably, Thatta has the highest annual incidence of suspected malaria in Sindh, estimated at approximately 191 cases per 1000 population.^28^ Transmission is characterised by two seasonal peaks: a smaller peak in March, coinciding with the onset of pre-monsoon rains, and a larger peak during the post-monsoon period from August to October, when increased rainfall and standing water provide favourable breeding conditions for Anopheles mosquitoes, the vectors of malaria. Both *Plasmodium vivax* and *P. falciparum* circulate in the area, with *P. vivax* accounting for most reported malaria cases. Trial activities will be carried out in one civil hospital in the district.

### Inclusion & exclusion criteria and recruitment

Inclusion criteria for the trial include: (a) women 6<20 weeks of gestational age, (b) Hb concentration of 70 g/L or higher; (c) willing to attend antenatal care (ANC) in the study clinics; and (d) willing to stop taking IFA and receive the study intervention. Age eligibility will vary by country. In Burkina Faso, we will include married or unmarried pregnant women aged ≥15 years; unmarried pregnant women aged 15–18 years will provide assent, with consent obtained from parents. In Pakistan, we will include married pregnant women ≥18 years. Exclusion criteria include (a) non-viable or extrauterine pregnancy and (b) any contraindications to iron- or calcium-containing supplements. In Burkina Faso, community sensitisation will be carried out in five antenatal care clinic catchment areas in the Kaya Health and Demographic Surveillance Site to promote booking pregnancies in the first trimester. Recruitment will take place when women come for routine antenatal care at one of these five clinics. Women will first see Ministry of Health staff for their exam, which includes a urine pregnancy test and fundal height measurement. Pregnant women with fundal height<22.5 cm will be referred to CaMMS offices adjacent to the antenatal care facility to undergo screening activities. In Pakistan, women will be identified via an ongoing pregnancy surveillance system, which is part of the multi-country Global Network for Women and Children’s Health Research.^29^ Research staff visit all married women of reproductive age to identify women who have missed a menstrual period and offer those women a urine pregnancy test. In addition, Community Informants can provide information on suspected pregnancies to these staff, prompting a household visit. Women with a positive urine pregnancy test who are interested will be accompanied to the Makli Civil Hospital for screening.

At both sites, trained research staff—trial midwives in Burkina Faso or research assistants in Pakistan—will describe the screening process and obtain written consent for screening activities. Following the screening procedures, described below, eligible women will be provided full information on the trial’s purpose, procedures, risks and benefits and will be asked to give their consent to participate using a trial-specific written consent form. In Burkina Faso, consent forms for both the screening activities and trial will be printed in French, the consent process will be conducted in French and a signature will be obtained. If the participant does not understand French or is illiterate, the consent form will be translated orally into the local language (Mooré), which is unwritten, and signed with the presence of a witness who will provide a signature. For unmarried 15–18 year-olds, permission will be obtained from a parent and then assent will be obtained from the adolescent. In Pakistan, written consent will be obtained using forms translated into Sindhi. If consenting women are illiterate, they will be asked to provide a thumb imprint on the consent form in the presence of an independent witness.

### Interventions

All participants will receive two daily supplements: (1) a UNIMMAP MMS, providing 30 mg elemental iron, and (2) a 500 mg elemental calcium supplement as 1250 mg calcium carbonate. In the intervention arm (the ‘together’ arm), women will be instructed to take both tablets together in the morning. In the control arm (the ‘separate’ arm), they will take MMS in the morning and calcium in the evening. Women in both arms will be told to take the supplements starting at enrolment (6<20 weeks’ gestation) until the end of the pregnancy.

UNIMMAP MMS will be sourced from Contract Pharmacal Corporation (Hauppauge, New York, USA). Calcium supplements will be sourced from CitraGen Pharmaceuticals (Fremont, California, USA). Bulk supplements will be co-packaged into arm-specific boxes (figure 1) by Remington Pharmaceuticals (Lahore, Pakistan), with barcoded labels to indicate lot numbers, the repackaging date, and the expiry date of repackaged supplements. Each box will contain four calendar blister packs with a 7-day supply of tablets. Study supplements will be stored in humidity and temperature-controlled pharmacies at each site until delivered to recruitment centres.

**Figure 1 F1:**
[figure not shown]
Images of CaMMS trial intervention boxes for (**A**) together arm and (**B**) separate arm. CaMMS, calcium and multiple micronutrient supplement.

As this trial compares two different supplement regimens (ie, taken together vs separately), adherence to the randomised regimen is essential to ensure the validity of the trial results. There is strong evidence that greater medication complexity (ie, multiple drugs, multiple times/day) reduces adherence.^30^ Thus, there is a risk of lower adherence in the arm allocated to separate doses, leading to potential bias. The trial will use a combination of packaging, counselling on key messages and adherence promotion via home visits and adherence partners to promote adherence to the allocated supplement regimen.

Human-centred design work carried out at both sites indicated that attractive packaging and a dedicated place to store supplements could encourage pregnant women to take pills. As calendar blister packaging has been shown to increase adherence compared with bottles,^31–33^ this strategy was also selected. Both boxes and blister cards will be marked to indicate whether women should take both supplements in the morning (marked with a sun icon) or to take the MMS in the morning and calcium in the evening (marked with a sun and moon and stars). The packaging will be explained to the woman at the enrolment visit and reinforced at follow-up visits as necessary.

Counselling cards with key messages, prompts and images were adapted from previous studies and revised based on pretesting of drafted materials and messages in interviews and focus groups. Key messages and adherence materials are available via Open Science Framework (https://doi.org/10.17605/OSF.IO/36W58). Cards will include counselling messages regarding how to take the supplements, adherence strategies and common barriers to adherence and how to address them. Study staff will deliver counselling messages to participants at the time the initial supplements are dispensed and will reinforce these messages at each subsequent visit. The counselling messages include other adherence strategies, such as the use of an ‘adherence partner’; taking the supplements at the same time and/or before/during/after a meal; and keeping the supplements in a visible place, such as the study-provided bag. In addition to centre-based counselling, either community health workers (Burkina Faso) or research staff (Pakistan) will visit women in their households to assess and support adherence, as described below.

### Assignment of interventions

The randomisation schema will be prepared by [name] and [name] using random permuted blocks with variable block size (4, 8 or 12) with a 1:1 allocation to the ‘together’ or ‘separate’ regimen, stratified by site and recruitment clinic. The list will include the sequence, country, health centre, randomly allocated intervention and unique participant identifier. An access-restricted, web-based, centralised allocation system covering both sites will be developed. Once a woman has provided consent for trial enrolment, the research staff will enter his or her valid username and password, the woman’s screening identification number and the enrolment date. They will then press the ‘Request New Allocation’ button and the system will reveal the next allocation to Separate or Together in the randomisation sequence, displaying the woman’s assigned 6-digit alphanumeric identification number.

### Outcomes

Our primary aim is to evaluate the effect of co-administered Ca and MMS on mean Hb concentration at 30<34 weeks of gestation, as measured by complete blood count (CBC).

Our secondary aims are to evaluate the effect of co-administered Ca and MMS on:

Iron status of pregnant women at 30<34 weeks of gestation (see table 1 for justifications): ferritin, soluble transferrin receptor (sTfR), hepcidin and erythropoietin (EPO) concentrations, as well as sTfR-ferritin index and hepcidin-EPO ratio; ferritin and sTfR will be presented with and without adjustment for inflammation.^34^Haematological status of pregnant women at 30<34 weeks of gestation: red blood cell count, mean corpuscular volume, mean corpuscular Hb and mean corpuscular Hb concentration.Hb concentration of infants within 72 hours of birth.Iron status of infants within 72 hours of birth.

**Table 1 T1:** Secondary iron status outcomes to be used in the CaMMS Trial

Outcome	Justification
Ferritin	Measure of storage iron; as inflammation increases ferritin and can mask true iron deficiency, data will be presented as unadjusted and adjusted using the BRINDA method^34^: Ferritin_adjusted_=ferritin_unadjusted_ – β_1_(CRP_obs_ – CRP_ref_) – β_2_(AGP_obs_ – AGP_ref_) – β_3_(malaria)
Soluble transferrin receptor (sTfR)	Measure of tissue iron demand for erythropoiesis; data will be presented both unadjusted and adjusted for inflammation: sTfR_adjusted_=sTfR_unadjusted_ – β_1_(CRP_obs_ – CRP_ref_) – β_2_(AGP_obs_ – AGP_ref_) – β_3_(malaria)
sTfR:log-ferritin ratio	Expressed to distinguish iron deficiency from apparent deficiency that occurs with inflammation; basis for calculation of total body iron stores
Hepcidin	Regulator of iron absorption; iron sufficiency and inflammation result in increased hepcidin and decreased iron absorption
Erythropoietin (EPO)	Endocrine signal for erythrocyte production
Hepcidin:EPO ratio	More sensitive measure of poor iron status, combining information regarding absorbed and circulating iron with extent of hypoxia

CaMMS, calcium and multiple micronutrient supplement; CRP, C-reactive protein.

Exploratory outcomes, defined as pre-specified outcomes not included in the confirmatory analysis and for which the trial was not powered to detect differences, include anaemia (Hb<110 g/L) at 30<34 weeks and, as an indicator of intervention safety, severe anaemia (Hb<70 g/L) at 20<24 weeks and 30<34 weeks of gestation. Other exploratory outcomes, defined in table 2, include iron deficiency, iron deficient erythropoiesis, iron deficiency anaemia, birth weight, LBW, gestational age at birth, weight-for-gestational age (GA) Z-score, small-for-gestational age, miscarriage and stillbirth.

**Table 2 T2:** Definitions of exploratory outcomes to be assessed in the CaMMS trial

Exploratory outcomes	Definition
Anaemia	Hb<110 g/L at 30<34 weeks of gestation
Intervention safety	Severe anaemia (Hb<70 g/L) at 20<24 weeks or 30<34 weeks
Iron deficiency	Plasma ferritin<15 µg/L at 30<34 weeks of gestation^*^
Iron-deficient erythropoiesis	sTfR concentration>8.3 mg/L at 30<34 weeks of gestation
Iron deficiency anaemia	Concurrent anaemia (Hb<110 g/L) and iron deficiency (plasma ferritin<15 µg/L)^1^ at 30<34 weeks of gestation
Birth weight	Infant weight within 72 hours of birth
Low birth weight	Infant weight<2500 g within 72 hours of birth
Gestational age (GA) at birth	GA at birth in weeks based on screening ultrasound and INTERGROWTH-21st standard
Preterm birth	GA at birth<37 weeks of gestation
Weight-for-gestational age Z-score	Calculated based on weight≤72 hour of birth using the INTERGROWTH-21st standard
Small-for-gestational age	<10th percentile of weight-for-gestational age using INTERGROWTH-21st standard
Miscarriage	Foetal loss <20 gestational weeks
Stillbirth	Foetal loss ≥20 gestational weeks

* An alternative physiologically based ferritin threshold of 25 µg/L will be used in sensitivity analyses based on recent evidence that this higher threshold may better identify individuals at an earlier stage of iron deficiency, when iron stores are insufficient for red blood cell production and other tissue functions.

CaMMS, calcium and multiple micronutrient supplement; Hb, haemoglobin ; sTfR, soluble transferrin receptor.

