### Biospecimen analysis

Venous blood collected at the early-pregnancy (6<20 weeks), mid-pregnancy (20<24 weeks) and late-pregnancy (30<34 weeks) visits will be stored on ice packs for shipment in EDTA-treated vacutainers and either untreated or serum separator vacutainers. In Burkina Faso, EDTA-treated whole blood will be sent to the Kaya District Hospital for full haematology analysis using a Sysmex MODEL XN-1000 haematology analyser (Sysmex Corporation, Kobe, Japan) and, at the baseline visit, qualitative testing for haemoglobinopathies by agarose electrophoresis on a cellulose acetate strip using a Wincom DY-300 Electrophoresis Machine (Wincom Company, Changsha, China). Ferritin and CRP will be measured using immunoturbidimetric assays on a Biolis 30i Automated Clinical Chemistry Analyzer (Tokyo Boeki Medical System, Tokyo, Japan). An aliquot of serum will be shipped on dry ice to the Micronutrient Laboratory at the Johns Hopkins Bloomberg School of Public Health, where commercial immunoassay kits will be used to measure sTfR (R&D Systems, Minneapolis, Minnesota, USA), hepcidin (DRG International, Springfield, New Jersey, USA), and EPO (R&D Systems, Minneapolis, Minnesota, USA). A commercial radial immunodiffusion assay (Kent Laboratories, Bellingham, Washington, USA) will be used to measure AGP.

In Pakistan, CBCs will be obtained using a Sysmex XN-100 automated haematology analyser (Sysmex Corporation, Kobe, Japan); haemoglobinopathies will be assessed by HPLC performed on a BIORAD Variant II instrument; and malaria parasitaemia will be assessed by microscopy on thick and thin blood smears. Both haemoglobinopathy and malaria testing will be done at baseline only in Pakistan, to inform ancillary analyses on the aetiology of anaemia in this setting. Ferritin, sTfR and CRP will be measured by immunoturbidimetric assay and AGP by immunological agglutination/turbidimetric assay on a Cobas c 311 Automated Analyzer (Roche Diagnostics GmbH, Mannheim, Germany), EPO will be measured using a chemiluminescent assay on the Immulite-2000 platform (Siemens Healthcare Diagnostics, Tarrytown, New York, USA), and hepcidin by a commercial competitive binding immunoassay (DRG Hepcidin 25 bioactive HS ELISA kit, DRG International, Springfield, New York, USA).

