**Figure 3 F3:**
[figure not shown]
Interpretation of noninferiority results from CIs using the fixed margins method. MMS, multiple micronutrient supplement.

If <10% of outcomes are missing due to losses to follow-up, specimen handling or testing considerations, or very preterm or extremely preterm birth prior to 30 weeks, we will perform multiple imputation by chained equations of missing outcome data using predictive mean matching to generate 50 complete datasets for ITT analysis.^46^ Multiple imputation has been proposed as a robust strategy to address outcome missingness in NI trials under the assumption that data are missing at random.^47^ Our imputation model will include, at minimum, treatment arm and covariates we have prespecified for inclusion in adjusted models. Multiple imputation will be performed within country to preserve site-specific data structures. Analyses will be repeated on each imputed complete dataset, and results will be pooled using Rubin’s method. We will conduct sensitivity analyses using inverse probability weighting to assess the robustness of conclusions to missingness if ≥10% of outcome data are missing.^48^

The analytic approach for secondary (table 1) and exploratory outcomes (table 2) will use ITT, PP and mITT to determine superiority of Ca and MMS taken together compared with Ca and MMS taken separately. We will use the same two-stage approach to analyse the countries separately and then pool country-specific treatment effects. For ferritin and soluble transferrin receptor, we will present results both unadjusted and adjusted for inflammation (CRP and AGP) using the methods published by Namaste *et al.*^34^ For binary outcomes, we will use log-binomial regression models with a log link and a binomial response distribution to estimate prevalence ratios with 95% CIs. P values will be adjusted for multiple comparisons using the Holm method, and statistical significance will be determined at α=0.05.

A full Statistical Analysis Plan is available at https://doi.org/10.17605/OSF.IO/36W58.

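### One absolute sTfR cut-off defines iron-deficient erythropoiesis in both countries although each country uses a different sTfR assay, so cases may be under- or over-counted in at least one of them

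*Protocol article*

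**What the plan says.** The protocol article, Outcomes, Table 2, defines iron-deficient erythropoiesis as "sTfR concentration>8.3 mg/L at 30<34 weeks of gestation". No country, assay or source is attached to the number.

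The Biospecimen analysis section describes two sTfR methods:

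- **Burkina Faso:** serum is shipped to a laboratory in the United States, where "commercial immunoassay kits will be used to measure sTfR (R&D Systems, Minneapolis, Minnesota, USA").
- **Pakistan:** "Ferritin, sTfR and CRP will be measured by immunoturbidimetric assay and AGP by immunological agglutination/turbidimetric assay on a Cobas c 311 Automated Analyzer".

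The Outcomes section classes this outcome among the exploratory ones, described as "pre-specified outcomes not included in the confirmatory analysis and for which the trial was not powered to detect differences". Under Statistical methods the binary outcomes follow the two-stage plan: "We will use the same two-stage approach to analyse the countries separately and then pool country-specific treatment effects". The model is also fixed there: "we will use log-binomial regression models with a log link and a binomial response distribution to estimate prevalence ratios with 95% CIs".

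A footnote to Table 2 provides a second threshold for ferritin ("An alternative physiologically based ferritin threshold of 25 µg/L will be used in sensitivity analyses"). There is none for sTfR.

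**The concern.** A concentration cut-off belongs to the assay and calibration on which it was set. Applied to two methods, it marks the same biological state on both only if both report on the same scale. The article does not say that they do, and describes no step that would make them so.

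This is more than a detail left to the analysis plan: the article states the operative rule (one number) and the two methods to which the rule is applied. Because sTfR has no alternative threshold, nothing in the stated analyses would reveal a mismatch.

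At stake are the prevalence reported for each country, the comparison of the two, the precision of the prevalence ratio in a country where few women exceed the cut-off, and the meaning of the pooled ratio.

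**Working it through.** **From the documents.** The cut-off is 8.3 mg/L (Table 2). It is stated, not derived, so there is no figure of the plan's to reproduce. With 1600 women per country and 15% loss (Sample size), 1600 × 0.85 = 1360 women are measured per country, 680 per arm.

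**Assumed, not in the documents.** sTfR is lognormal with geometric mean GM and log SD s on the scale to which the cut-off belongs. The other assay reads k times that scale.

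**Prevalence read on the other assay.** The cut-off acts as 8.3/k on its own scale:

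prevalence = 1 − Φ[(ln(8.3/k) − ln GM)/s]

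At k = 1, GM = 6, s = 0.4: (ln 8.3 − ln 6)/0.4 = 0.811, and 1 − Φ(0.811) = 20.9%.

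**Precision.** With the same prevalence p in both arms, the SE of the log prevalence ratio is √[2(1 − p)/(680p)].

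| k | Effective cut-off (mg/L) | Prevalence read | Women of 1360 | SE of log ratio |
|---|---|---|---|---|
| 1.25 | 6.64 | 40.0% | 544 | 0.07 |
| 1.0 | 8.30 | 20.9% | 284 | 0.11 |
| 0.9 | 9.22 | 14.1% | 192 | 0.13 |
| 0.8 | 10.38 | 8.5% | 116 | 0.18 |
| 0.7 | 11.86 | 4.4% | 60 | 0.25 |

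The ratio detectable with 80% power at two-sided 5%, before the Holm adjustment, is about exp(2.80 × SE): 1.34 at k = 1 and 2.03 at k = 0.7.

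**Range.** Over GM 5 to 7 and s 0.3 to 0.4, the share of cases missed at k = 0.7 runs from 72% to 96%. At k = 1.25 the count is inflated by a factor of 1.6 to 3.8. Setting the true prevalence directly (10% to 40%) with s from 0.3 to 0.5, the share still detected is [1 − Φ(z(1−p) + ln(1/k)/s)]/p. That gives 51% to 80% at k = 0.9, 21% to 61% at k = 0.8 and 7% to 42% at k = 0.7. Half the cases are lost once k falls to somewhere between 0.90 and 0.75. In the other direction, a true 20% reads as 35% to 46% at k = 1.25.

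**Effect on the pooled ratio.** Suppose, again as an assumption, that the together arm raises sTfR by 10% in both countries (GM 6 to 6.6, s = 0.4). At k = 1 the prevalence ratio is 28.3%/20.9% = 1.36. At k = 0.7 it is 7.15%/4.43% = 1.61. The same biological effect thus yields two ratios because the effective cut-offs differ, and pooling would average them under one label.

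**The case against.** The strongest reply is that the documents show no scale difference at all. They do not say which assay 8.3 mg/L comes from or how the two methods compare, and every k above is assumed. That stands. It limits the point to a risk whose size and direction are unknown.

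A reader might go further in three ways that the documents do not support.

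- **That in one country the rule misses most cases.** This needs a particular k below 1. In the illustration at k = 0.9, 192 of 284 cases (68%) are still counted, and over-counting is as possible as under-counting.
- **That a real rise in the together arm would go unseen.** Both arms within a country share assay and cut-off, so the randomised comparison is not biased towards either. Continuous sTfR is itself a secondary outcome, analysed by country. With the assumed 10% rise, its comparison gives z = ln(1.1)/(0.4 × √(2/680)) = 4.4 whatever k is. Even the binary outcome gives z of about 3.2 at k = 1, 2.1 at k = 0.7 and 1.6 at k = 0.6. That is lost precision, not blindness.
- **That the model could not be fitted.** A log-binomial model with allocation as its only term fits whenever both arms have events. At k = 0.6 in the illustration there are still about 25 cases.

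It can also be said that the outcome is exploratory and that the separately posted protocol and analysis plan may settle the matter. The first lowers the severity. The second is possible, but Table 2 as published states a single number.

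**Conclusion.** The point holds as a minor one. The plan applies one absolute cut-off to two different sTfR assays and states neither an assay-specific limit nor a conversion. If the assays differ in scale, women are misclassified in at least one country. With GM 6 mg/L and log SD 0.4, a true 20.9% would be reported as anything from 4.4% (k = 0.7) to about 40% (k = 1.25). If they agree, nothing is lost. These figures rest wholly on assumed values of GM, SD and k.

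The damage is confined to the reported prevalence, its comparison between countries, the precision of the country-specific ratio and the pooled ratio, which would mix two effective definitions. The unbiasedness of the within-country comparison, the continuous sTfR outcome and the haemoglobin non-inferiority decision are not affected.

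**What to change.** In Table 2, state which assay the 8.3 mg/L limit belongs to. Define iron-deficient erythropoiesis as sTfR above the assay-specific upper limit of the method used in that country, and name both limits before unblinding.

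The cost is a change of wording and two limits; no new participants, visits or samples are needed. The downside is that the cut-off is no longer one number across countries. The documents also do not show that two manufacturers' limits mark the same state in pregnancy, so the pooled ratio should carry that caveat.

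Running a set of stored sera on both methods and converting one scale to the other would keep a single cut-off. It costs extra assay runs and probably further shipment, since the article describes sending serum abroad only from Burkina Faso. It is not needed to resolve this point.
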